**Figure 1 F1:**
[figure not shown]
Flow diagram of participants through the trial.

### Outcome measures

#### Main outcome measure

The primary outcome is the percent difference in 6-month breastfeeding exclusivity rates between the intervention and control groups.

### Secondary outcome measures

Differences between the two groups with respect to the following:

a) Breastfeeding exclusivity rates at 1 and 3 months.

b) Breastfeeding rates (exclusive or mixed feeding) at 1, 3 and 6 months.

c) Breastfeeding knowledge and attitudes of mothers at 6 months.

d) Success of a mother-to-mother support system measured as satisfaction rates of BFMis, SMs, and lactation experts; BFMi referral rates and adverse events during the 6 months.

e) Cost-benefit and cost-effectiveness analyses of the complex intervention.

f) Maternal quality of life at 1, 3 and 6 months using the validated Postpartum Quality of Life (QoL) questionnaire [30].

g) Success of mothers in exclusively breastfeeding new babies, measured as the percent difference between the intervention and control groups in 6-month breastfeeding exclusivity rates of subsequent babies, up to 5 years following the intervention.

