**Methods/Design:**

A multi-center randomized controlled trial. *Study population*: 443 healthy pregnant women in their first trimester will be randomized to control or intervention group. *Intervention*: A “prenatal/postnatal” professional and peer breastfeeding support package continuing till 6 months postpartum, guided by the Social Network and Social Support Theory. Control group will receive standard prenatal and postnatal care. Mothers will be followed up from early pregnancy till five years after delivery. *Outcome measures*: Total and exclusive breastfeeding rates, quality of life at 1, 3 and 6 months postpartum, maternal breastfeeding knowledge and attitudes at 6 months postpartum, maternal exclusive breastfeeding rates of future infants up to five years from baseline, cost-benefit and cost-effectiveness analyses of the intervention. *Statistical analysis*: Descriptive and regression analysis will be conducted under the intention to treat basis using the most recent version of SPSS.

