### Sample size

The most recently reported 6-month exclusive breastfeeding rate in Lebanon is 2% [23], which is the expected rate in the control group. The complex intervention is hypothesized to increase the 6-month exclusivity rate in the intervention group to 12%. To detect this 10% difference between the two groups with 90% power and 5% type I error, 155 mothers are needed per group. Allowing for a loss-to-follow up rate of 30%, the needed sample size becomes 443 women. The number of SMs to be recruited is 74, assuming that each support mother will pair with 3 breastfeeding mothers from the intervention group.

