### Statistical methods

We will compare continuous variables using Student’s *t* test and categorical variables using Chi square test. The relationship between breastfeeding exclusivity as outcome and the independent variables (maternal age, study group, socio-economic status, maternal education, study site, pediatrician’s gender, type of delivery, baby’s gender, parity, previous breastfeeding, maternal employment, mother’s religion, baseline breastfeeding knowledge and attitude, baseline social support) will be explored in bivariate and multivariate analysis. Regression models will be built to adjust for possible confounding in the relationship between the dependent and the independent variables stated above. All analysis will be done on intention to treat basis. The Statistical Package for Social Sciences (SPSS) will be used for data management and analyses. A p-value of <0.05 will indicate statistical significance.

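### Quality of life is measured in the same women at months 1, 3 and 6, but the only stated method that reaches it is a t test, which at month 6 makes no use of earlier scores from women lost in between

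*Protocol article*

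**What the plan says.** Under Secondary outcome measures, item (f) compares the arms on "Maternal quality of life at 1, 3 and 6 months". The Data collection section lists quality of life for participant mothers at those three times and not at baseline.

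The Statistical methods section opens with a general rule: "We will compare continuous variables using Student’s *t* test". The regression models that follow have one outcome: "The relationship between breastfeeding exclusivity as outcome and the independent variables". The same section adds "All analysis will be done on intention to treat basis" and "A p-value of <0.05 will indicate statistical significance". The abstract says only "Descriptive and regression analysis will be conducted under the intention to treat basis", without naming a model for quality of life. No repeated-measures method and no adjustment for several tests is named anywhere in the article.

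The Sample size section is the source for the expected loss: "Allowing for a loss-to-follow up rate of 30" per cent, which takes the total to 443 women.

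**The concern.** Three scores from the same woman are correlated, so an early score carries information about a later one that is missing. A separate t test at each visit cannot use that link. At month 6, a woman with scores at months 1 and 3 who is then lost contributes nothing.

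Three things are at stake:

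- **Precision.** The month-6 comparison is less precise than the collected data allow.
- **Bias.** If the reasons for loss relate to earlier quality of life in one arm more than in the other, the comparison of women still present at month 6 is distorted. A likelihood-based repeated-measures model corrects for this when loss depends on observed scores.
- **Several tests.** Three tests at 0.05 with no visit named as the main one allow a claim on whichever visit reaches significance.

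The protocol gives quality of life some weight. It appears in the abstract, has its own associated sub-study, and is named in the Discussion among the study's strengths.

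**Working it through.** **Inputs from the protocol.** Visits at months 1, 3 and 6; no baseline score; 30% loss; 155 per group and 443 in total; 0.05 per test.

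**Assumed inputs.** The protocol gives no standard deviation or between-visit correlation for quality of life. The correlation ρ is therefore varied over 0.3 to 0.7.

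**1. The plan's own figure.** For 2% against 12%, 90% power and two-sided 5%, the pooled formula gives 135 per group, and with continuity correction 155. Then 2 × 155 / (1 − 0.30) = 442.9, so 443. Both stated numbers reproduce. If the planned loss occurs, about 310 of 443 women have month-6 data.

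**2. Precision at month 6, one earlier score used.** Take the variance with full data as 1.

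- Complete cases: 1/0.7 = 1.429.
- Using the earlier score: (1 − ρ²)/0.7 + ρ².
- Ratio of the second to the first: 1 − 0.3ρ².

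| ρ | Variance using earlier score | Reduction, all loss after a score | Reduction, half the loss before month 1 |
|---|---|---|---|
| 0.4 | 1.360 | 4.8% | 2.8% |
| 0.5 | 1.321 | 7.5% | 4.4% |
| 0.6 | 1.274 | 10.8% | 6.4% |
| 0.7 | 1.219 | 14.7% | 8.6% |

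The last column allows for women lost before they have any score. If 15 of every 100 women go before month 1 and 15 afterwards, the missing share among women with a score is 15/85 = 17.6%, and the reduction is 0.176ρ².

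**3. Precision with both earlier scores.** Assume equal correlation between visits and all loss after month 3. Months 1 and 3 together explain R² = 2ρ²/(1 + ρ) of the month-6 score, and the variance ratio is 1 − 0.3R². For ρ = 0.3, 0.5 and 0.7 the ratio is 0.96, 0.90 and 0.83. Then 155 completers per arm carry the information of about 162, 172 and 187. This is the most favourable pattern of loss.

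**4. Bias, by simulation.** Set a true effect of 0.30 SD and 30% loss in each arm, all after month 3.

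- Loss driven by month-3 quality of life in the control arm only (log odds of 1 per SD, lower scores more likely lost): the month-6 difference among women still present is 0.23, 0.17 and 0.12 SD for ρ = 0.3, 0.5 and 0.7. The likelihood estimate stays at about 0.30.
- Loss driven by it equally in both arms: both methods give about 0.30.

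**5. Three tests at 0.05.** If independent, the chance of at least one false positive is 1 − 0.95³ = 14.3%. For equally correlated test statistics it is 12.5% at 0.5, 11.8% at 0.6 and 10.9% at 0.7.

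**The case against.** The strongest reply is that the Statistical methods section never mentions quality of life. Its opening sentence is a general one in a condensed article, and quality of life has its own sub-study, whose plan is not shown and may name a suitable model. It stands that the t test reaches this outcome only through a general rule. But that rule is stated, the regression models are tied to breastfeeding exclusivity, and nothing else in the article applies to a continuous outcome. The point improves a stated method and does not complain that detail is absent.

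Four stronger readings are tempting, and the documents do not support them:

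- **That the t tests throw away the early scores.** Scores of women lost later still enter the month-1 and month-3 tests. Only the month-6 comparison makes no use of them.
- **That t tests are unbiased only when loss is unrelated to quality of life.** When loss depends on it equally in both arms, the arm difference was about right in the simulation. The harmful pattern is dependence that differs by arm. The arms do differ in contact: intervention women receive home visits, a hotline and peer support. That makes the pattern conceivable, but nothing in the protocol shows that it will occur.
- **That the plan contradicts its intention-to-treat statement.** A t test at each visit can compare women as allocated, and the mixed model also omits women with no score.
- **That a single overall arm effect must be the main test.** An average over the three visits is a different target and could hide an early effect that fades. Naming one visit, or a joint test, is equally defensible.

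The 30% loss also runs from enrolment in pregnancy. With no baseline score, women lost before month 1 cannot be recovered by any such model, so the upper end of the precision gain is a best case.

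**Conclusion.** The point holds as a minor, inexpensive improvement. The per-visit t test is a legitimate analysis but uses the month-6 data less well than it could. Using one earlier score, the month-6 variance would fall by about 5 to 15% if all loss follows a score, and by about 3 to 9% if half the loss precedes month 1, for assumed correlations of 0.4 to 0.7. Bias is a possibility that depends on loss related to earlier quality of life differently by arm; the simulated sizes illustrate it and are not predictions. The false-positive chance of about 11 to 12.5% applies if any one of the three visits may be claimed. The primary outcome and the sample size are unaffected.

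**What to change.** State that quality of life will be analysed with one linear mixed model for repeated measures instead of separate t tests: arm, visit, arm-by-visit interaction and site as fixed effects, unstructured covariance across the three visits, and all women with at least one score, as randomised. Report the arm difference and 95% interval at months 1, 3 and 6. Name in advance either one visit or a joint test across visits as the main quality-of-life comparison.

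The cost is a sentence or two in the plan and slightly more analysis work. The model can be fitted in the planned software and needs no new data and no baseline score. It relies on loss being missing at random given the observed scores, which should be said. If the sub-study plan already contains such a model, a reference to it in the main protocol is enough.

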### Recruitment

Trained recruiters will be present all day in the obstetric clinics at both sites, based on a specified schedule that is agreed upon with the obstetricians, depending on availability of clients. The study recruiter will identify eligible subjects visiting the clinics and approach them directly for participation in the study. She will explain the details and the procedure of the study, and check eligibility as per the inclusion and exclusion criteria. Subjects will be given the informed consent forms to read at leisure and will be encouraged to ask questions. They will also be given the recruiters telephone number should they wish to call later for consent or questions. Women will be interviewed in the privacy of a specified space dedicated for the study interviewers in each clinic.

### Data collection

#### Participant mothers

1. *Baseline:* Age, socio-economic status, education, employment status, mother’s religion, baseline breastfeeding knowledge and attitude, parity, previous breastfeeding, baseline social support, study site, residence.

2. *Month 1:* Baby’s gender, mode of delivery, pediatrician’s gender, first feed at hospital, rooming in, breastfeeding status, baby’s illness visits (number, diagnosis, money spent on medicine and doctor’s fees), baby’s hospitalizations (number, diagnosis, cost), days lost from work due to baby’s illness, days lost from work due to mother’s illness, cost of formula feeds/week, cost of water used to prepare formula/week, mother’s non-routine doctor visits due to breastfeeding, cost of infant food/week, QoL.

3. *Month 3:* Breastfeeding status, baby’s illness visits (number, diagnosis, money spent on medicine and doctor’s fees), baby’s hospitalizations (number, diagnosis, cost), days lost from work due to baby’s illness, days lost from work due to mother’s illness, cost of formula feeds/week, cost of water used to prepare formula/week, mother’s non-routine doctor visits due to breastfeeding, cost of infant food/week, QoL.

4. *Month 6:* Breastfeeding status, baby’s illness visits (number, diagnosis, money spent on medicine and doctor’s fees), baby’s hospitalizations (number, diagnosis, cost), days lost from work due to baby’s illness, days lost from work due to mother’s illness, cost of formula feeds/week, cost of water used to prepare formula/week, mother’s non-routine doctor visits due to breastfeeding, cost of infant food/week, QoL, satisfaction of mother with mother-to-mother support system, breastfeeding knowledge and attitude of mother, in-depth interviews with BFMis.

5. *Year 1:* Breastfeeding status, baby’s illness visits (number, diagnosis, money spent on medicine and doctor’s fees), baby’s hospitalizations (number, diagnosis, cost), days lost from work due to baby’s illness, days lost from work due to mother’s illness, cost of formula feeds/week, cost of water used to prepare formula/week, mother’s non-routine doctor visits due to breastfeeding, cost of infant food/week.

6. *Year 2:* Breastfeeding status, baby’s illness visits (number, diagnosis, money spent on medicine and doctor’s fees), baby’s hospitalizations (number, diagnosis, cost), days lost from work due to baby’s illness, days lost from work due to mother’s illness, cost of formula feeds/week, cost of water used to prepare formula/week, mother’s non-routine doctor visits due to breastfeeding, cost of infant food/week, breastfeeding status of new baby.

7. *Year 3:* Baby’s illness visits (number, diagnosis, money spent on medicine and doctor’s fees), baby’s hospitalizations (number, diagnosis, cost), days lost from work due to baby’s illness, breastfeeding status of new baby.

8. *Year 4:* Baby’s illness visits (number, diagnosis, money spent on medicine and doctor’s fees), baby’s hospitalizations (number, diagnosis, cost), days lost from work due to baby’s illness, breastfeeding status of new baby.

9. *Year 5:* Baby’s illness visits (number, diagnosis, money spent on medicine and doctor’s fees), baby’s hospitalizations (number, diagnosis, cost), days lost from work due to baby’s illness, breastfeeding status of new baby.

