3. Support mothers: Training of SMs will take place at AUBMC at an agreed upon time and place. One of 3 pediatricians -part of the research team- will conduct seven training workshops. Each workshop consists of two 2-hour sessions and will include a maximum of 10 SM participants. The first of the 2 sessions will be mainly theoretical. It will entail a brief overview of the mother-to-mother support program and training on the LOVE (listen observe validate empower/educate) method of support. In the second part of the first session, *breastfeeding basics* will be discussed, including advantages of breast milk and risks of formula; common culture-specific misconceptions will be addressed and proper technique of breastfeeding will be demonstrated using visual aid material. Breastfeeding trouble-shooting, and criteria for referral to appropriate medical services will also be emphasized. These criteria aim to identify mothers with medical conditions such as mastitis or breast abscess and postpartum depression or psychosis as well as infant medical conditions, such as hyperbilirubinemia and/or dehydration. During the second session, which will be largely practical, support mothers will be asked to review what they have learned through interactive discussions; they will engage in role playing of “*what if*” scenarios as necessary, including failure to breastfeed scenarios. For those specific cases, SM’s empathy and positive attitude will be emphasized. They will subsequently be handed a small manual containing a list of local breastfeeding resources as well as their telephone log sheets and activity records.

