### Cost analysis

The economic efficiency of breastfeeding promotion will be investigated through the assessment of the costs incurred during 1 year by families feeding their infants artificial milk versus breastfeeding (whether exclusive or mixed). The analysis will take into consideration the cost of planning and implementing the Complex Intervention for Breastfeeding Promotion initiative and the various costs associated with healthcare provision, nutrition and lost productivity during one year for families in both study groups. The cost analysis will test whether the economic burden of exclusive breastfeeding is less than partial breastfeeding, and less than formula feeding at the family level, as well as at the national level. We will explore the association between the infant feeding status (exclusive breastfeeding, partial breastfeeding, formula feeding), and study group (intervention/control) as independent variables, and the following dependent variables: non routine doctor visits, hospitalization, work absences due to infant sickness, work absences due to mother sickness, cost of formula milk, cost of water used for formula preparation, mother’s non-routine doctor visits related to breastfeeding, lost productivity of parents due to breastfeeding, and cost of other infant foods.

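### The mother's doctor visits count only if due to breastfeeding and her hospital admissions are not listed, so the cost comparison by feeding status and study group omits other maternal care

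*Protocol article*

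**What the plan says.** All references are to the protocol article.

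- **Data collection, Participant mothers.** At Months 1 and 3 the list includes the mother's "non-routine doctor visits due to breastfeeding, cost of infant food/week, QoL". The same item, with the same restriction by cause, stands at Month 6, Year 1 and Year 2. No maternal hospitalization is listed at any contact.
- **Same section, infant items.** The infant's "illness visits (number, diagnosis, money spent on medicine and doctor’s fees" are recorded, as are the infant's "hospitalizations (number, diagnosis, cost". Neither is limited by cause.
- **Same section, another maternal item.** At the same five contacts the list has "days lost from work due to mother’s illness", which is not tied to breastfeeding.
- **Secondary outcome measures.** These include "BFMi referral rates and adverse events during the 6 months" and "Maternal quality of life at 1, 3 and 6 months using the validated Postpartum Quality of Life (QoL) questionnaire".
- **Training details, support mothers.** Among the conditions that should prompt referral are "mastitis or breast abscess and postpartum depression or psychosis as well as infant medical conditions".
- **Cost analysis.** Feeding status and study group are the independent variables. The dependent variables include the mother's "non-routine doctor visits related to breastfeeding, lost productivity of parents due to breastfeeding". The section sets out to test whether exclusive breastfeeding carries a lower economic burden than partial breastfeeding or formula feeding, over one year.

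**The concern.** A comparison of economic burden between feeding groups needs components that can take any value in each group. This one cannot do so freely. A visit enters the data only if it is put down to breastfeeding, so the chance of its being counted depends on the exposure under comparison. A mother who is not breastfeeding has little opportunity to contribute to the item, however much care she uses.

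Two things are at stake. The first is the fairness of the cost comparison: maternal care that non-breastfeeding mothers use is largely uncharged, while similar care in a breastfeeding mother may be charged. The second is content. The protocol cites lower postpartum depression as a benefit of both breastfeeding and lay support, and it trains support mothers to recognise depression. Yet a doctor visit or admission for depression would normally fall outside the only maternal healthcare-use item.

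**Working it through.** The plan gives no figure on this point, so the check is a comparison of the text followed by a short identity in symbols.

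**Step 1. Infant and maternal items side by side (Participant mothers).**

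| | Infant | Mother |
|---|---|---|
| Doctor visits | illness visits, any diagnosis | only those due to breastfeeding |
| Detail listed for visits | number, diagnosis, money spent | none |
| Hospital admissions | number, diagnosis, cost | no item |
| Work days lost to illness | any cause | any cause |

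The plan therefore uses all-cause counting for the infant and for maternal work loss, but not for maternal visits.

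**Step 2. Where the item is used.** It is listed at five contacts: Months 1, 3 and 6, Year 1 and Year 2. The cost analysis covers one year, so four of the five fall within its horizon. The Cost analysis section names nine dependent variables, and the maternal visit item is one of them. Its first two variables, doctor visits and hospitalization, do not say whose they are. The data list could supply them only for the infant.

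**Step 3. What the restriction does.** For each feeding group, let B be the mean number of maternal non-routine visits per mother attributed to breastfeeding, and O the mean number of all others. Let b stand for breastfeeding mothers and f for formula-feeding mothers.

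- True difference: (B_b + O_b) − (B_f + O_f)
- Recorded difference: B_b − B_f
- Recorded minus true: O_f − O_b

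The error is zero only if the unrecorded visits are equally frequent in both groups. There are two ways in which they would not be.

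1. *Other illness differs.* If mothers who do not breastfeed use more care for other causes, O_f exceeds O_b and the recorded difference makes breastfeeding look more costly than it is.
2. *Attribution differs.* Suppose both groups make the same number V of visits. A share a_b is attributed to breastfeeding in one group and a smaller share a_f in the other. The true difference is 0, but the recorded difference is (a_b − a_f) × V, which is positive.

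Because O is not collected, the trial could not check either possibility. Unlisted maternal admissions produce an error of the same form in the cost total.

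**Step 4. Feeding status versus study group.** The same identity holds between arms, with error O_control − O_intervention. Randomization makes equal other-cause care more plausible there, unless the intervention itself changes it. The attribution route remains if one arm contains more breastfeeding mothers. The comparison by feeding status is the more exposed of the two.

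**Step 5. Whether other planned items fill the gap.**

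- *Adverse events and referrals.* These are stated outcomes, but no adverse-event item is in the listed data. Under Process evaluation, referral runs through support mothers, so it has no control-arm counterpart.
- *Quality of life.* Collected at Months 1, 3 and 6. It yields no visit, admission or cost.
- *Work days lost to maternal illness.* All-cause and in both arms, but informative mainly for employed women, and with no healthcare use or cost.

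None of these supplies O, maternal admissions or their costs in both arms.

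**The case against.** The strongest reply is that this is a cost variable and not a safety instrument. If the intervention leads to more breastfeeding, and breastfeeding to more visits for breastfeeding problems, those visits are a real incremental cost and should be counted. All-cause counts would add noise from unrelated visits. Mastitis, abscess, depression and psychosis appear as referral criteria, not as trial outcomes. A journal article's variable list is also not the case report form.

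Much of this stands. Breastfeeding-related visits are a real cost and should still be reported. The missing diagnosis and cost sub-fields, taken alone, are weak evidence, because an article commonly leaves such detail to the full protocol. The restriction by cause is different: it is a positive definition, repeated at five contacts and carried into the Cost analysis section. Counting a real cost of breastfeeding does not make the comparison fair if maternal care for other causes is left out of every feeding group.

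A reader might go further and infer three things that the document does not support:

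- *That this item is the plan's sole record of maternal harm, so the named conditions cannot be counted at all.* Adverse events, referrals, quality of life and work days lost are also planned. The supportable statement is narrower: the listed variables do not allow those conditions to be counted by type and compared between arms.
- *That formula-feeding mothers score zero by definition.* Every enrolled woman intends to breastfeed, and one now using formula may have had a breastfeeding-related visit before or around stopping. The item is biased towards zero for her, not fixed there.
- *That the excess can be computed by multiplying an assumed any-cause visit rate by assumed breastfeeding rates.* That treats every visit by a breastfeeding mother as recorded by the item, which its wording excludes.

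**Conclusion.** The point holds as a defect in one cost variable. The only maternal healthcare-use item is restricted by a cause bound up with the exposure, no maternal admission item is listed, and the item is then compared by feeding status and study group. The likely direction is against breastfeeding. This assumes that mothers who do not breastfeed use at least as much other-cause care, or that breastfeeding mothers attribute more of the same visits to breastfeeding. If other-cause care were equal and attribution did not differ, the visit difference would be undistorted, although total maternal burden would still be understated.

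The size cannot be given, because the document contains no maternal visit or admission rates. The reach is one of nine cost variables, plus maternal admissions. The primary outcome and the sample size of 443 are unaffected. The change should be made, but the trial's main conclusion does not depend on it.

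**What to change.** In both arms, at Months 1, 3 and 6 and Years 1 and 2, replace the item with all of the mother's non-routine doctor visits and hospitalizations, each with number, diagnosis and cost, mirroring the infant items. In the Cost analysis section, use all-cause maternal counts and costs in the comparisons by feeding status and study group, and state there that doctor visits and hospitalization cover mother and infant separately. Report the breastfeeding-related subset as a secondary breakdown, classified from the recorded diagnosis and not from the mother's own attribution. This keeps the information that the present item was meant to give.

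The cost is a reworded question at contacts already planned, slightly longer interviews, and some added noise from unrelated visits. It needs no extra visit and no change in sample size.
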